### 10.2 Secondary study parameter(s)

#### *Maximal acetylcarnitine concentrations*

Acetylcarnitine concentrations before and after exercise will be presented quantitatively in mmol/kgww. Differences between time-points (pre and post exercise) will be analyzed with a paired sampled T-test. Pearson correlation coefficients will be computed to correlate with parameter values such as insulin sensitivity and metabolic flexibility.

#### *Metabolic compounds*

Time effects of metabolites in plasma (i.e. glucose, free fatty acids, triglycerides, cholesterol, insulin) will be presented quantitatively and analyzed using a two way ANOVA repeated measures analysis for analyzing data over time.

*Skeletal muscle mRNA and protein levels at baseline and during insulin stimulation*

Skeletal muscles parameters of the carnitine mechanism (such as CrAT activity and acetylcarnitine profiles) as well as lipid intermediates will be analyzed comparing pre and post clamp values using a paired sampled T-test. Differences between intervention arms (LIPID+CAR, LIPID+PLAC, SALINE+PLAC) will be analyzed with a one way ANOVA for repeated measured with post-hoc analysis if data allow to do so.

### **10.3 Other study parameters**

Not applicable.

### **10.4 Interim analysis (if applicable)**

An interim analysis will be performed after 3 subjects have completely performed the entire study in order to confirm that the carnitine infusion model upon lipid induced insulin resistance works. It is known that type 2 diabetic patients are characterized by insulin resistance and metabolic inflexibility and that these characteristics are absent in young lean healthy subjects. Infusion of lipids in these young lean healthy subjects results in insulin resistance and decreased metabolic flexibility as in type 2 diabetic patients. This is characterized by a decrease in glucose infusion rate, glucose oxidation and increased fat oxidation rate during the clamp. Carnitine is suggested to rescue metabolic inflexibility and insulin resistance which would result in higher glucose infusion rates, glucose oxidation and decreased fat oxidation upon lipid infusion. To assure that carnitine indeed reaches the muscle we will check whether we see the expected patterns in substrate oxidation with or without addition of carnitine upon lipid infusion, and thus the model used in this study is adequate to answer our research question, we are performing an interim analysis after 3 subjects have completely performed the entire study (all three clamps). During the interim analysis, no new subjects will perform any test days before the results of the interim analysis is known. In case no changes occur in glucose infusion rate or substrate oxidation, the study will not be continued, as in that case, the study set-up is not suited to investigate the molecular mechanisms underlying the beneficial effects of carnitine.

## **ETHICAL CONSIDERATIONS**

### **10.5 Regulation statement**

This study will be conducted according to the principles of the Declaration of Helsinki (64th WMA General Assembly, Fortaleza, Brazil, October 2013) and in accordance with the Medical Research Involving Human Subjects Act (WMO). The study will be conducted in compliance with International Conference on Harmonization Good Clinical Practice. The study will be approved by local medical ethics committee and local authorities before start of the study.

### **10.6 Recruitment and consent**

Subjects will be recruited by means of posters, advertisements in local papers and online (appendix E3) or by contacting subjects from earlier studies, provided that they gave consent for this. Subjects that are interested will be contacted by telephone by a member of the research team. During this telephonic interview the study protocol and the inclusion criteria will be briefly explained to the subjects and some of the basic inclusion criteria will be checked (e.g. gender, age, weight, height, BMI, sports participation, general health, dietary habits, MRI contra-indications and being vegetarian). When the subjects are interested, they will receive the detailed subject information via mail or e-mail or personally. They will be instructed to read it carefully and to ask questions when things are unclear. If desired, subjects can contact an independent physician or their own physician. After about 1 week of consideration, the subject is contacted again if he gave permission for this. Permission to contact the subject again after one week of consideration will be asked during the telephonic interview. If the subject wants to participate after reading the information, they are invited for screening. Before the start of the screening, an informed consent form will be signed and dated by the subjects as well as a member of the research team in duplicate. One form for the researcher and one form for the subject.

### **10.7 Objection by minors or incapacitated subjects (if applicable)**

Not applicable.

### **10.8 Benefits and risks assessment, group relatedness**

This study carries no benefits for the subjects and carries minor risks for the subjects. The major burdens consist of a moderate time commitment and multiple (6) muscle biopsies. During visit 4, visit 5 and visit 6 we will take frequent blood samples with a maximum of 176mL, which can be dangerous in case of anemia. This is why subjects with low hemoglobin levels are excluded from participation to minimize this risk. The total amount of

blood taken in the entire study will maximally be 538 mL divided over minimal one month. Blood samples are taken via vena puncture or an intravenous cannula. There is a risk of pain, minor bleeding, bruising or inflammation of the sites of the cannulas on the arm. State of the art techniques, measures of sterility and trained personnel minimize these risks. During the anesthesia and muscle biopsies of the upper leg, subjects will experience some pressure and sometimes pain of a short duration. Due to the anesthesia, the procedure will be almost always painless. There is a small risk of infection or prolonged bleeding of the muscle biopsy site. Infections or continued bleeding on the other hand are very rare. To minimize these risk, subjects using anti-coagulants are excluded from the study. A hematoma can develop after taking the biopsy. Sometimes, numbness of small skin-area may persist for some time after the biopsy, due to damaging small cutaneous nerves. The skin incision will result in a small scar (~ 5 mm). To promote good wound healing, the incision will be sealed with sterile steri-strips and a waterproof band-aid. After taking the biopsy compression to the biopsy site will be applied manually and with a compression bandage to minimize bleeding. State of the art technique, measures of sterility and trained personnel will minimize the before mentioned burdens and risks. Furthermore, the risks will be lower in healthy young subjects. After the biopsies, subjects will experience some muscle pain for 2-3 days. Hyperinsulinemic euglycemic clamping is a procedure we perform routinely in our laboratory without notable complications. In rare occasions subjects exhibit symptoms of hypoglycemia (even if their blood glucose levels are still above 3 mmol/l). After successfully performing the clamp procedure, blood glucose values will be monitored for an additional 60 minutes with glucose infusion stand-by, in case glucose levels happen to drop. Solid food and sugar-containing drinks will be provided directly after finalizing the clamp to avoid the experience of hypoglycemia.

We do not expect that co-infusion of lipids will be harmful to the subjects in the study because the lipid are administrated in a physiological dose of 540ml (108 gram of lipid) which is far below the maximal allowed dosage of 3 gram fat per kg body weight (For a individual of 70 kg this equals 210 grams of fat, much higher than the administration in this study). There is a small risk of headache, changes in body temperature, tiredness, nausea or vomiting. All side effects are reversible after discontinuation of treatment. In 2006 a comparable lipid infusion study was performed in our research team with healthy young and lean subjects (METC20063049). These subjects received a comparable dosage of Intralipid for 6 hours during a hyperinsulinemic euglycemic clamp, and no complications occurred. This also indicates that the combination of Intralipid with insulin, glucose and tracer glucose is well tolerated.

We do not expect that co-infusion of carnitine will be harmful to the subjects in this study as the human body excretes any surplus via the urine. Carnitine is administered in a dose (28mg/kg body weight/day) which is below the maximal allowed dosage of 30mg/kg body weight/day. There is a small risk of nausea, fishy odor, vomiting or diarrhea. Carnitine infusion is a procedure performed more often in research studies without notable complications [6,7,15,17]. Stephens et al. [6] also performed carnitine infusion during a hyperinsulinemic euglycemic clamp for 6 hours. More than double carnitine concentrations (10mg/kg/h) compared to this study were administered to the subjects without complications.

This also indicates that the combination of carnitine with insulin, glucose and tracer glucose is not harmful.

Carnitine in combination with Intralipid is previously investigated by Natali et al. (1993) [20] and no complications were reported. As already noticed before carnitine infusion during a hyperinsulinemic euglycemic clamp as well as Intralipid infusion during a hyperinsulinemic euglycemic clamp were previously performed without noted complications. Therefore, the combination of providing Intralipid and Carnitine together during a hyperinsulinemic euglycemic clamp is not expected to be harmful.

MRS is a safe procedure, with no known health risk as long as none of the exclusion criteria are met. The maximal cycling test and cycling protocol can cause muscle soreness.

Measurements performed during the time course of the study can potentially lead to unexpected medical findings. Subjects will be informed about such a finding and possible advised to contact a doctor about this. If a subject does not want to be informed about incidental findings, participation in this study is not possible.

This study will lead to novel insights in the potential beneficial effects of L-carnitine infusion to improve lipid induced insulin resistance and metabolic flexibility. This is expected to have a major impact on our understanding of the muscle metabolism physiology and development and progression of type II diabetes mellitus (T2DM), which will ultimately contribute to new and improved strategies for the prevention, monitoring and therapy of T2DM.

### **10.9 Compensation for injury**

The sponsor/investigator has a liability insurance which is in accordance with article 7 of the WMO.

The sponsor has an insurance which is in accordance with the legal requirements in the Netherlands (Article 7 WMO and the Measure regarding Compulsory Insurance for Clinical Research in Humans of 23th June 2003). This insurance provides cover for damage to research subjects through injury or death caused by the study.

1. € 650.000,-- (i.e. six hundred and fifty thousand Euro) for death or injury for each subject who participates in the Research;
2. € 5.000.000,-- (i.e. five million Euro) for death or injury for all subjects who participate in the Research;
3. € 7.500.000,-- (i.e. seven million and five hundred thousand Euro) for the total damage incurred by the organisation  
for all damage disclosed by scientific research for the Sponsor as  
'verrichter' in the meaning of said Act in each year of insurance coverage.

The insurance applies to the damage that becomes apparent during the study or within 4 years after the end of the study.

**10.10 Incentives (if applicable)**

Subject will be compensated for time investment and the burden of the study, The compensation is based upon the time spent at the university (€8 per hour spent during normal work time according to minimum wage) and the amount of muscle biopsies (€15 per biopsy). After complete participation, the total compensation will be €402. Premature termination of the study protocol will result in a reduced compensation relative to the duration of the participation.

| Day   | Time spent at the university | Financial compensation (Euro) |
|--------------|-------------------------------------|--------------------------------------|
| Visit 1      | 1 hours                             | 8                                    |
| Visit 2      | 1 hours                             | 8                                    |
| Visit 3      | 2.5 hours                           | 20                                   |
| Visit 4      | 11 hours                            | 88                                   |
| Visit 5      | 11 hours                            | 88                                   |
| Visit 6      | 11 hours                            | 88                                   |
| Food diary   | 1.5 hours (at home)                 | 12                                   |
| Total | 39 hours                     | 312                           |

Subjects will receive an extra financial compensation of €15 for donating one muscle biopsy. Because 2 muscle biopsies are taken (pre and post clamp) at visit 4, visit 5 and visit 6 (in total 6 biopsies) an extra financial compensation of €90 will be provided.

**The total financial compensation for the entire study will therefore be €402.**

Subjects will not be compensated for the screening only. Subjects will receive compensation for travelling costs, with a maximum of 19 cents per kilometer.

## **11. ADMINISTRATIVE ASPECTS, MONITORING AND PUBLICATION**

### **11.1 Handling and storage of data and documents**

All data will be handled confidentially and coded (concordant with the “wet bescherming persoonsgegevens; WBP”). This means that the study results and human material will be related to a code/number and not to the name, initials or birth-date of the subject. Before the start of the screening, subjects will be assigned a study code that will not change during the study. The code is linked with the name, date of birth and contact-information of the subject in a protected file. Only members of the research team, health inspection (IGZ), METC or monitors can access this file. For all other purposes, the code will be used for subject identification. Furthermore, subjects will be given the opportunity to obtain information regarding their study results. This information will be given verbally or in writing. All blood samples and biopsies taken from the subjects will be stored for 15 years for further analyses in line of this research. Approval will be asked from the subjects on the informed consent form. For future analyses in the line of the current study, approval will be asked again to the METC. The retention period for the research data will be 15 years and only researchers directly involved in the research will have the possibility to access these data. Subjects will be asked in the informed consent form if they may be contacted again for future research.

### **11.2 Monitoring and Quality Assurance**

Not applicable.

### **11.3 Amendments**

A ‘substantial amendment’ is defined as an amendment to the terms of the METC application, or to the protocol or any other supporting documentation, that is likely to affect to a significant degree:

- the safety or physical or mental integrity of the subjects of the trial;
- the scientific value of the trial;
- the conduct or management of the trial; or
- the quality or safety of any intervention used in the trial.

All substantial amendments will be notified to the METC and to the competent authority.

Non-substantial amendments will not be notified to the accredited METC and the competent authority, but will be recorded and filed by the sponsor.

#### **11.4 Annual progress report**

The sponsor/investigator will submit a summary of the progress of the trial to the accredited METC once a year. Information will be provided on the date of inclusion of the first subject, numbers of subjects included and numbers of subjects that have completed the trial, serious adverse events/ serious adverse reactions, other problems, and amendments.

#### **11.5 Temporary halt and (prematurely) end of study report**

The sponsor will notify the accredited METC and the competent authority of the end of the study within a period of 90 days. The end of the study is defined as the last patient's last visit.

The sponsor will notify the METC immediately of a temporary halt of the study, including the reason of such an action.

In case the study is ended prematurely, the sponsor will notify the accredited METC and the competent authority within 15 days, including the reasons for the premature termination.

Within one year after the end of the study, the investigator/sponsor will submit a final study report with the results of the study, including any publications/abstracts of the study, to the accredited METC and the Competent Authority.

#### **11.6 Public disclosure and publication policy**

Publication policy is in agreement with the CCMO publication statement. The results of the study will be published in peer-reviewed scientific journals. Both positive and negative results of the study will be disclosed.

## 12. STRUCTURED RISK ANALYSIS

### 12.1 Potential issues of concern

#### a. Level of knowledge about mechanism of action

The mechanism of the beneficial effects of carnitine are not fully understood, we propose that increased availability of carnitine improves the capacity to form acetyl-carnitine in insulin resistant subjects, thereby increasing the capacity for postprandial glucose oxidation also known as improved metabolic flexibility (see introduction and rationale in research protocol).

#### b. Previous exposure of human beings with the test product(s) and/or products with a similar biological mechanism

L-carnitine for intravenous infusion was used in many clinical studies in similar concentrations than we propose here [6,7,14 and Appendix D2).

#### c. Can the primary or secondary mechanism be induced in animals and/or in ex-vivo human cell material?

Animal research showed indeed that carnitine availability can be limiting in insulin sensitivity and metabolic inflexibility that developed due to high fat exposure (see introduction and rationale) and that addition of carnitine can reverse this. This data is the basis of this research proposal.

#### d. Selectivity of the mechanism to target tissue in animals and/or human beings

Carnitine is a natural compound in skeletal muscle and other tissues of the human body. When consuming a western style diet, availability of free carnitine was shown to decline, especially in insulin resistant subjects who show lower carnitine levels. We hope to reverse this by providing an intravenous L-carnitine infusion in the insulin resistant state (due to lipid infusion).

#### e. Analysis of potential effect

The highest carnitine dose administered in this study equals 28 mg/kg. This does not exceed the maximal allowed dosage of 30mg/kg/day.

#### f. Pharmacokinetic considerations

Carnitine is secreted in urine and is usually reabsorbed in the kidneys to a large extent (up to 95% reabsorption in case of low carnitine status), leaving room to regulate plasma carnitine levels also by reducing reabsorption. L-Carnitine tubular reabsorption exhibits typical characteristics of a carrier-mediated process, including saturation kinetics at high plasma concentrations. The efficiency of the tubular reabsorption of L-carnitine increases as dietary intake decreases in order to maintain circulating L-carnitine concentrations within a narrow normal range. On the other hand, when L-carnitine concentrations increase, such as with exogenous administration via infusion of L-carnitine, greater urinary loss takes place. This shows that oversupply of carnitine is very unlikely because excess of carnitine can be excreted by the kidneys. As elimination of excess carnitine is depending on a normal kidney function, subjects with plasma concentrations of creatinine higher than 115 micromol/l will be

excluded from the study. There have been no reports of toxicity from L-carnitine overdosage. L-carnitine is easily removed from plasma by dialysis. The half-life of release of carnitine from skeletal muscle is estimated to be 139 hours.

g. Study population

The study population consists of young (18-40 years) healthy subjects with a normal body weight (BMI:18-25 kg/m^2). The study is restricted to males to prevent hormonal influences of the menstrual cycle and known gender differences in metabolism. Earlier studies with L-carnitine infusion were performed on the same population ([6] + appendix D2).

h. Interaction with other products

Reports of INR increase with the use of warfarin (anti-coagulant) have been observed. It is recommended that INR levels be monitored in patients on warfarin therapy after the initiation of treatment with L-carnitine or after dose adjustments. To prevent interaction we excluded subjects taking anti-coagulants. Furthermore, no interactions with other products are observed.

i. Predictability of effect

The appearance of side-effects (nausea and diarrhea) cannot be predicted. Transient nausea and vomiting have been observed. Less frequent adverse reactions are body odor, nausea, and gastritis.

j. Can effects be managed?

Effects will vanish when the infusion of the L-carnitine is discontinued.

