### 4.2 Inclusion criteria

In order to be eligible to participate in this study, a subject must meet all of the following criteria:

- Caucasian
- Healthy (as determined by responsible physician based on a medical questionnaire)
- Male
- Age: 18-40 years
- Normal BMI: 18-25 kg/m^2
- Stable dietary habits
- No use of medication interfering with investigated study parameters (as determined by responsible physician)

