### 4.3 Exclusion criteria

A potential subject who meets any of the following criteria will be excluded from participation in this study:

- Female
- Haemoglobin levels < 7.8 mmol/L
- Uncontrolled hypertension
- Use of anticoagulants
- Engagement in exercise > 3 hours a week
- Being vegetarian or vegan (because of altered whole body carnitine status)
- Smoking
- Alcohol and/or drug abuse
- Unstable body weight (weight gain or loss > 5kg in the last 3 months)
- Significant food allergies/intolerances (seriously hampering study meals)
- Participation in another biomedical study within 1 month before the first study visit, which would possibly hamper our study results
- Medication use known to hamper subject's safety during the study procedures
- Medication use known to interfere with investigated study parameters
- Subjects with contra-indications for MRI
- Subjects who intend to donate blood during the intervention or subjects who have donated blood less than three months before the start of the study
- Subjects who do not want to be informed about unexpected medical findings
- Subjects who do not want that their treating physician is informed

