### 5.2 Use of co-intervention (if applicable)

Subjects are advised to continue their normal eating pattern during the time of the study, so no change in macronutrient composition of the diet is necessary. Intake of red meat is allowed. Subjects are also advised to maintain their normal living-, activity-, and sleeping pattern. However, 3 days prior to any of the test days, the subjects will be asked to withstand from alcohol and refrain from strenuous physical activity in order to not confound any of the outcome measures. The dietary habits will be registered during the 3 days preceding the clamp with a food diary. Furthermore, they will be asked to consume a standardized meal ("macaroni bolognaise") the evening before all three hyperinsulinemic euglycemic clamps

(visit 4,5,6) followed by an overnight fast. During the hyperinsulinemic euglycemic clamp subjects will be administrated to a lipid co-infusion in two out of three trial arms

L-carnitine should not be administrated in case of renal insufficiency, therapy with anticoagulants, pregnancy or breast feeding.

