### 8.3 Study procedures

#### Screening

Eligibility for participation in the study will be checked via a telephonic interview prior to inviting subjects for a screening visit at the university. During this telephonic interview the study protocol will be verbally explained to the subjects and some of the basic inclusion and exclusion criteria will be checked, such as weight, height, BMI, age, sports participation, general health, dietary habits, MRI contra-indications and being vegetarian. When the subjects are still interested in participation in the study and fulfil the basic inclusion criteria, they will receive the detailed subject-information by e-mail or mail accompanied with a general brochure (provided by the Dutch government) about participating in a medical study. The subject will be instructed to read it carefully, and to ask questions when things are unclear. Permission to contact the subject again after one week of consideration will be asked during the telephonic interview. If subjects are still willing to participate after reading the information, an appointment for signing informed consent and a screening visit will be made. For this screening visit, subjects will come to the university in the morning after an overnight fast (from 10PM). Before the start of the screening, an informed consent form will be signed and dated by the subjects as well as the researchers in duplicate. One form for the researcher and one form for the subject. The screening visit will include:

- A medical history questionnaire (Appendix F1.1)
- A MRI contra-indication questionnaire (Appendix F1.2)
- Answering questions about lifestyle such as eating and sporting habits (subjects lifestyle should be consistent with in- and exclusion criteria).
- Measurement of length, body weight (E1200, August Sauter, GmbH, Albstadt, Germany) and waist circumference
- Blood pressure
- Electrocardiogram (evaluated by a responsible physician or a colleague appointed by him)
- A fasted blood draw (to determine general health with parameters such as hemoglobin and potassium)

The duration of the entire screening visit will be 1 hour. Only if all the results from the screening visit are in compliance with our in- and exclusion criteria, subjects can participate in the study.

Body composition (Bod Pod)

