## **12.2 Synthesis**

L-Carnitine for intravenous infusion is a registered medical product and administration with the proposed dosage is considered safe (SPC L-carnitine: appendix D2) and was used in multiple human studies with similar dosage in similar subject populations.

To limit the appearance of side-effects (nausea and diarrhea), subjects will be screened for renal dysfunction because in these subjects the capacity for homeostatic regulation of carnitine is hampered. The risk of developing side effects in subjects with normal renal function is small and considered acceptable as these are no serious side-effects which can easily be relieved by stopping the L-Carnitine infusion.

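### The renal exclusion stated in the risk analysis is missing from the eligibility lists and from the named screening blood tests, so those sections would allow enrolment of a subject whom the risk analysis excludes

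*Protocol*

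**What the plan says.** Three places in the protocol treat kidney function as a condition for receiving L-carnitine.

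- Section 12.1(f), Pharmacokinetic considerations, gives the reason, "As elimination of excess carnitine is depending on a normal kidney function", and then the rule: "subjects with plasma concentrations of creatinine higher than 115 micromol/l will be" excluded from the study (the sentence finishes after a page break).
- Section 12.2, Synthesis, says that "subjects will be screened for renal dysfunction because in these subjects the capacity for homeostatic regulation of carnitine is hampered". It goes on to call the risk of side effects small and acceptable where renal function is normal.
- Section 5.2 says that "L-carnitine should not be administrated in case of renal insufficiency, therapy with anticoagulants, pregnancy or breast feeding".

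Three other places determine who enters the trial.

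- Section 4.2 requires a subject to be "Healthy (as determined by responsible physician based on a medical questionnaire").
- Section 4.3 opens with "A potential subject who meets any of the following criteria will be excluded from participation in this study" and lists 17 items. The only laboratory limit among them is "Haemoglobin levels < 7.8 mmol/L".
- Section 8.3, Screening, lists "A fasted blood draw (to determine general health with parameters such as hemoglobin and potassium"), and then allows participation only if the screening results agree with the inclusion and exclusion criteria.

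**The concern.** A numerical exclusion limit appears in the risk analysis and nowhere else. The sections that a study team works from when deciding eligibility carry neither the limit nor the test needed to apply it. If those sections are followed literally, a man with creatinine above 115 micromol/l meets no listed reason for exclusion, and no named test would reveal his value.

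What is at stake is mainly safety. The protocol itself argues that surplus carnitine is harmless because healthy kidneys remove it, and it cites renal screening when it judges the risk acceptable. A safeguard used in that argument should be visible in the sections that put it into effect. There is also a matter of conduct: an eligibility rule stated in one part and absent from another can be applied differently from subject to subject.

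**Working it through.** There is no figure to reproduce. The check is a comparison of the sections.

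**Step 1: where a renal rule is stated.**

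| Section | Renal content | Limit | Test named |
|---|---|---|---|
| 12.1(f) | Exclusion from the study | Creatinine above 115 micromol/l | Plasma creatinine |
| 12.2 | Screening for renal dysfunction | None | None |
| 5.2 | L-carnitine not to be given in renal insufficiency | None | None |

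**Step 2: where eligibility is decided.**

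| Section | Renal content |
|---|---|
| 4.2 Inclusion criteria | None; health is judged from a medical questionnaire |
| 4.3 Exclusion criteria | None among 17 items |
| 8.3 Screening | None; haemoglobin and potassium are given as examples |
| 3 Study design, Visit 1 | None; this shorter description mentions no blood test |

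Creatinine occurs only in 12.1(f). The similar word in the spectroscopy part of 8.3 is creatine, the internal reference signal, and has nothing to do with kidney function.

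**Step 3: follow one candidate through.** Take a man who satisfies every item in 4.2, meets none in 4.3, and has creatinine above 115 micromol/l. Under 8.3 his named results agree with the criteria, so nothing there stops him. Under 12.1(f) he is excluded. The sections give different answers for the same man.

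**Step 4: compare with the protocol's other safeguards.**

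- Anticoagulants: 12.1(h) relies on excluding users, and 4.3 lists the exclusion.
- Anaemia: the benefit and risk assessment (10.8 in the body) relies on excluding men with low haemoglobin. Section 4.3 gives a limit and 8.3 names the test.
- Kidney function: 12.1(f) and 12.2 rely on exclusion and screening. Section 4.3 gives no limit and 8.3 names no test.

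The first two safeguards are carried into the operative sections and the third is not. That pattern suggests an omission in drafting rather than a decision to leave the criterion out.

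**The case against.** The strongest reply is that a protocol is read as a whole. Section 12.1(f) is protocol text and states the exclusion without condition. Section 12.2 promises the screening, and 5.2 bars the product in renal insufficiency. Agreement with the listed criteria is written in 8.3 as a necessary condition for participation, not a sufficient one, so it does not cancel an exclusion stated elsewhere. The two named blood tests are examples, and creatinine may well be measured alongside them. The medical questionnaire, which is not shown, may ask about kidney disease.

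Much of this stands. A reader might infer that the renal check can never operate, or that the trial would in fact enrol men with raised creatinine. The document does not support either inference, for the reasons just given. What it supports is that 4.2, 4.3 and 8.3 as written would allow such enrolment. An open list of examples does not require the assay, a questionnaire does not produce a creatinine value, and staff working from the eligibility lists have no limit to apply.

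Two further inferences should be resisted.

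- A reader might expect men to be removed after inclusion on creatinine grounds, with consequences for the analysis. Screening comes before inclusion, 12.1(f) would support an exclusion at that stage, and nothing in the protocol points to a later one.
- A reader might gauge the problem by the gap between the stated total dose of 28 mg/kg and the stated daily maximum of 30 mg/kg. No section links that gap to kidney function, so it does not measure this issue.

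It is also fair to say that the safety argument does not rest on renal screening alone. Section 12.2 also cites the product's registration, earlier human use at similar dosage, and side effects that are not serious and are relieved by stopping the infusion.

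**Conclusion.** The inconsistency is real and can be seen from the text alone. Section 12.1(f) states an exclusion, and 12.2 a screening step, that 4.2 and 4.3 do not contain and 8.3 does not name. As a result, the sections used to decide eligibility would allow a subject whom the risk analysis says is excluded.

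Its size cannot be calculated. The protocol gives no distribution of creatinine and no proportion above 115 micromol/l. That few healthy men aged 18 to 40 would exceed the limit is an assumption, though a reasonable one. With 13 subjects planned, the number concerned could easily be zero. The primary comparison, its power and its error rate do not depend on the point.

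The conclusion assumes that the questionnaire and the other appendices not shown do not supply the missing criterion. Even if they did, 4.3 and 8.3 would still be out of step with 12.1(f). The correction should be made because it is cheap and bears on subject safety.

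**What to change.** Reconcile 4.3, 5.2, 8.3, 12.1(f) and 12.2 so that the eligibility list, the named screening tests and the risk analysis all state the same renal rule. What that rule should be, including whether it carries a numerical limit, is for the responsible physician to decide; this review takes no position on it.

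The cost is a short text change in the affected sections. Section 11.3 requires notification to the ethics committee and the competent authority if the change is judged a substantial amendment; otherwise it is recorded and filed. If the creatinine rule is kept, it also needs one assay on the 10 mL screening sample that Appendix 2B already provides for. The design, sample size and analysis need no change on this account.
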